## **Outline of Research**

### **1. Objective**

To investigate the relationship between dietary status, type of intestinal bacteria, and equol-producing ability.

To examine the effects of ingestion of "equol + lactobionic acid" on various parameters of lifestyle-related disease risk such as arteriosclerosis and visceral fat area including the relationship with the above background factors.

### **2. Research population**

Postmenopausal women who undergo medical examinations at the Sendai General Health Screening Clinic.

### **3. Methods**

Subjects: Healthy postmenopausal women aged 50 years or older who undergo a medical examination at the above facility and who have consented to this study.

Period: August 2017-February 2018

Supplement: "Equol-containing fermented soybean" and "Lactobionic acid-containing fermented lactose" foods(Contains S-form equol 10 mg / day and lactobionic acid 150 mg / day)

Survey contents: Equal production ability test by urinalysis, intestinal bacteria test by stool test, eating habit assessment survey by self-administered questionnaire, menopausal symptom questionnaire, general biochemical test by blood sampling, visceral fat area measurement by visceral fat CT test (fat scan) , AGE value measurement by AGE reader, pulse wave velocity measurement

Timing of investigations: At the start of the survey, and every month, at the end of the survey (12 weeks later)

### **4. Research period and estimated sample size**

Research period: August, 2017 to February 2018

Estimated sample size: 60 women

## **Outline of clinical trial on equol and lactobionic acid supplement**

### **1. Research Objective and Background**

Equol is an active metabolite in which daidzein, a type of soy isoflavone, is metabolized by intestinal bacteria. Its structure is similar to that of the female hormone estrogen, and it has an estrogen-like action, which alleviates menopausal symptoms. , Suppression of bone loss, improvement of lipid metabolism and arteriosclerosis, etc. have been reported, and are expected to be effective for a wide range of women's health care.

On the other hand, the number of people who can produce equol in the body is as small as about 50% in Japan, and it is said that the eating habits, living environment, and intestinal bacteria, which are equol-producing bacteria, are involved in the equol-producing ability.

In this clinical study, it is considered meaningful to investigate and clarify the relationship between dietary habits and the types of intestinal bacteria regarding equol-producing ability.

In addition, we investigated the effects of ingestion of "equol + lactobionic acid" on lifestyle-related disease parameters such as vascular system, visceral fat area, and AGEs (advanced glycation end products) in the above subjects, and investigated the effects of equol production ability and intestinal bacteria. It is important to clarify the relationship with the background factors of equol in order to further build evidence on the action of equol.

### **2. Research Population**

#### **1) Target person**

Those who have recruited subjects from postmenopausal\* healthy women aged 50 years or older who wish to undergo a medical examination at the Sendai General Medical Examination Clinic and have obtained their consent to participate in this study.

\* Menopause is spontaneous menopause, excluding menopause due to invasion such as surgery.

#### **2) Selection, exclusion, discontinuation criteria**

##### **① Selection criteria**

Those who meet all of the following selection criteria and have the ability to consent are eligible.

- Japanese healthy postmenopausal women over 50 years old
- Persons undergoing medical examination at Sendai General Clinic
- Persons who can undergo interviews or examinations at the start of the examination and every month at the Sendai General Clinic (8 minutes on foot from JR Sendai Station)
- Person who can take the recommended quantity of supplement and record daily life diary during the implementation period (12 weeks)

##### **② Exclusion criteria**

Persons with a history of allergies to soy foods, dairy products, and brewer's yeast.

- Persons who have started taking medicines or health foods that may have an effect during the test period.

- Those who are receiving HRT or who are taking drugs that may act on hormones.
- Others that the investigating doctor deems inappropriate.

### ③Cancellation criteria

Clinical research will be discontinued if any of the following applies.

- During the test period, the subject develops serious symptoms and the safety of the supplement becomes questionable.
- When it becomes clear that the subject was affected by continuously consuming the supplement.

### 3) Registration

- The principal investigator will register the candidate as a subject after confirming that she meets the eligibility criteria and does not meet any of the exclusion criteria.

## 3. Method

- 1) Survey period: 12 weeks (August 2017-February 2018)
- 2) Test method: Epidemiological survey, clinical trial (randomized open trial)
- 3) Number of cases: 60 cases (30 women who take equol + lactobionic acid supplement, and 30 women who do not take the supplement)
- 4) Test food: "Equol + lactobionic acid" 3 tablets (10 mg) daily (marketed in December 2013)

## 4. Measures

Before ingesting the supplement: Equol check (in urine), gut microbiota test (stool test), dietary habit assessment (BDHQ).

Before and after ingestion of supplement: height / weight / body composition, blood test (TG, HDL-C, LDL-C, T-CL, uric acid, HbA1C), baPWV, visceral fat CT test (fat scan), AGE measurement by AGE reader, and climacteric system assessments.

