## 5. Outcome evaluation

- 1) Primary Outcomes: blood test (TG, HDL-C, LDL-C, T-CL, uric acid, HbA1C), baPWV, visceral fat area
- 2) Key Secondary Outcomes: AGE, relationship between equol-producing ability, type of intestinal bacteria, and dietary habit assessment (BDHQ) from the test results, safety of supplement, climacteric symptoms

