## 6. Schedule

|                                | One week before | Week 0 | Week 4 | Week 8 | Week 12 | Result report |
|--------------------------------|-----------------|--------|--------|--------|---------|---------------|
| Explanation and consent        | ⊙               |        |        |        |         |               |
| Urine equol test               |                 | ○      |        |        |         | ⊙             |
| Intestinal flora test          |                 | ○      |        |        |         | ⊙             |
| Dietary questionnaire          |                 | ○      |        |        |         | ⊙             |
| Blood test                     |                 | ○      |        |        | ○       | ⊙             |
| baPWV                          |                 | ○      |        |        | ○       | ⊙             |
| Body weight measurement        |                 | ○      |        |        | ○       |               |
| Visceral fat scan              |                 | ○      |        |        | ○       | ⊙             |
| AGE reader                     |                 | ○      |        |        | ○       | ⊙             |
| Supplement                     |                 | ←————→ |        |        |         |               |
| Climacteric symptom assessment |                 | ○      | ○      | ○      | ○       |               |
| Safety monitoring              |                 | ○      | ○      | ○      | ○       |               |

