## 7. Analysis

For the primary measures, perform chi-squared test and t test for comparison between groups and before and after the study period. For secondary outcomes, anonymized data are entered into the database and the correlation is analyzed. Drop out cases and missing values are not included in the analysis. Other questionnaire surveys will be conducted according to the evaluation criteria of each questionnaire. The visceral fat CT examination and baPWV measurement at the start of the test and at 12 weeks will be performed at the same site in order to eliminate measurement errors.

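### Equol-producing ability rests on one week-0 urine test with no stated soy intake beforehand, so its correlation with diet could be partly spurious

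*Protocol*

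**What the plan says.** The first objective in the Outline of Research is "To investigate the relationship between dietary status, type of intestinal bacteria, and equol-producing ability". Section 5 repeats it as a key secondary outcome, the "relationship between equol-producing ability, type of intestinal bacteria, and dietary habit assessment (BDHQ) from the test results". Section 7 gives the method: "For secondary outcomes, anonymized data are entered into the database and the correlation is analyzed".

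Ability is measured in urine. The Outline (3. Methods) lists it as "Equal production ability test by urinalysis". Section 4 places it before supplementation, with the stool test and the diet questionnaire: "Before ingesting the supplement: Equol check (in urine), gut microbiota test (stool test), dietary habit assessment (BDHQ"). In the section 6 table the row "Urine equol test" is marked at week 0 and at no other visit. Section 17 names the commercial kit and its supplier.

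On the biology, section 1 says: "Equol is an active metabolite in which daidzein, a type of soy isoflavone, is metabolized by intestinal bacteria". It also says that "the number of people who can produce equol in the body is as small as about 50% in Japan".

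The protocol does not mention a soy portion or diet instruction before the sample, a record of recent soy intake, a cut-off, a daidzein-corrected result or a repeat test. The eligibility criteria in section 2 exclude soy allergy but do not standardise soy intake. In the section 6 table the visit one week before is used only for explanation and consent.

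**The concern.** On the protocol's own account, equol appears only if two things are present: the bacteria, and daidzein for them to act on. A single urine sample therefore reflects both a woman's capacity and what she has recently eaten. Soy intake is also part of the dietary status with which the result will be correlated.

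The classification error would thus depend on the exposure under study. A producer who ate little soy is more likely to be missed, and she is more likely to be found among the low soy eaters. An association between diet and ability could then appear when diet has no influence on ability, and a larger sample would not remove it. The correlation of bacteria with ability would be weakened, because some carriers would be counted as non-producers. Any reading of supplement effects by producer status, which the second objective mentions as a background factor, would carry the same error.

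**Working it through.** **The protocol's own figure.** No figure in the protocol bears on the accuracy of the urine test, so there is none to reproduce. The check is an illustration of direction and possible size.

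**Inputs from the protocol**
- True ability: about 50% (section 1), taken as equal in low- and high-soy women, so there is no real association.
- Number of women: 60 (section 3).

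**Assumed inputs**
- q, the share of women with no recent soy before the sample: 10% vs 0%, 20% vs 5% and 40% vs 5% in low- vs high-soy women.
- A producer with no recent soy tests negative; every other woman tests correctly.
- For counts, two diet groups of 30, so 15 true producers in each. These are diet groups, not the randomised arms.

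**Formulas**
- Apparent producer share p = 0.5 × (1 − q).
- Spurious odds ratio = [p(high) / (1 − p(high))] / [p(low) / (1 − p(low))].
- True producers missed = 15 × q(low) + 15 × q(high).

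**Results**

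| q low vs high | p low | p high | Odds ratio | Producers missed, of 30 |
|---|---|---|---|---|
| 10% vs 0% | 0.450 | 0.500 | (0.500/0.500)/(0.450/0.550) = 1.22 | 1.5 + 0 = 1.5 |
| 20% vs 5% | 0.400 | 0.475 | (0.475/0.525)/(0.400/0.600) = 1.36 | 3 + 0.75 = 3.75, about 4 |
| 40% vs 5% | 0.300 | 0.475 | (0.475/0.525)/(0.300/0.700) = 2.11 | 6 + 0.75 = 6.75, about 7 |

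The true odds ratio is 1.0 in every row.

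**Chance of a significant result.** For 30 vs 30 women and a two-sided 5% Pearson chi-squared test, I summed the binomial probabilities of all tables that reject. The three rows give about 7%, 9% and 28%. With no misclassification the figure is about 5%.

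**A second parametrisation.** Suppose the test detects 95% of producers among adequate soy eaters, and 90%, 70%, 50% or 30% among low soy eaters (all assumed). The observed share is then 47.5% against 45%, 35%, 25% or 15%, and the spurious odds ratio is 1.11, 1.68, 2.71 or 5.13. With 15 low soy eaters among the 60, the chance of a significant result is about 5%, 13%, 34% or 66%. The bias is negligible if the test hardly depends on intake and large if it depends strongly on it.

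**After the fix.** If detection does not depend on soy intake and is complete in both groups, the apparent share is 50% in both, the odds ratio is 1.0, and the rejection rate returns to about 5%.

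**The case against.** The strongest reply is that this argues from silence about a kit that cannot be seen. Section 17 assigns the test to a named commercial product. Its instructions may require soy beforehand, or it may report equol relative to daidzein. Preparation advice could also be given at the consent visit. This stands: the documents do not show that diet before the sample is uncontrolled in practice, nor that a woman without substrate is classed as unable, since no producer definition is given. They show only that the protocol does not say how this is handled.

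It also stands that every no-soy share above is assumed, and that in the milder cases a spurious association would seldom reach significance with 60 women. A reader might infer that a false diet association will appear; the documents support only that it could. A reader might also infer that the supplement comparison is compromised. It is not: the primary outcomes are compared between randomised groups without using producer status, and section 7 specifies no analysis of supplement effects by producer status.

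The suggestion that this can wait for a statistical analysis plan does not stand. Analysis rules can be set there, but conditions of sample collection cannot. If recent soy intake is neither arranged nor recorded, it cannot be recovered later. The diet questionnaire is described as an assessment of habit, not as a record of what was eaten before the sample.

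**Conclusion.** The point holds as a weakness in how a key secondary outcome, and the first-listed objective, is measured. The protocol fixes ability by one week-0 urine test, states that the measured substance is formed from a dietary substrate, and correlates the result with diet without arranging or recording that substrate. Unless the kit deals with this, the diet correlation could be partly spurious and the bacteria correlation diluted.

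The direction follows from section 1 of the protocol; the size does not follow from the documents. Under the three assumed scenarios the spurious odds ratio runs from 1.22 to 2.11. In the 20% vs 5% case with equal diet groups, about 4 of 30 true producers are missed. The randomised comparison of primary outcomes is unaffected.

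**What to change.** At the existing visit one week before, instruct every woman to eat the same standard portion of an ordinary soy food before the week-0 urine collection, following the kit's instructions where they specify this. Record at week 0 whether she did. If the kit already requires soy or corrects for daidzein, say so in section 4.

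Base the diet and bacteria analyses of producer status on women with confirmed intake, whether their urine result is positive or negative, and repeat them in all women as a sensitivity analysis. Setting aside only unconfirmed women who test negative would be selection on the result, and could itself produce an association with diet.

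The cost is one instruction, one question and one analysis rule, with no new visit or test. A few women may drop out of this secondary analysis because their intake is not confirmed.

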## 5. Outcome evaluation

- 1) Primary Outcomes: blood test (TG, HDL-C, LDL-C, T-CL, uric acid, HbA1C), baPWV, visceral fat area
- 2) Key Secondary Outcomes: AGE, relationship between equol-producing ability, type of intestinal bacteria, and dietary habit assessment (BDHQ) from the test results, safety of supplement, climacteric symptoms

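### Eight unranked primary outcomes, tested both between groups and before versus after, with no statement of which result decides the trial

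*Protocol*

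**What the plan says.** Protocol section 5 (Outcome evaluation) lists: "Primary Outcomes: blood test (TG, HDL-C, LDL-C, T-CL, uric acid, HbA1C), baPWV, visceral fat area". That is six blood measures plus baPWV and visceral fat area, eight in all, with no order among them.

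Protocol section 7 (Analysis) says how they are tested: "For the primary measures, perform chi-squared test and t test for comparison between groups and before and after the study period". It names two kinds of test and two kinds of comparison for the primary measures as a group. It does not say which test goes with which measure, whether before-after is tested in one arm or both, or which result settles the question.

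Section 3 (Method) describes the design as a "clinical trial (randomized open trial" with "60 cases (30 women who take equol + lactobionic acid supplement, and 30 women who do not take the supplement". No significance level, sidedness, effect size or power appears anywhere in the protocol. The outline gives the number of women only as an estimate: "Estimated sample size: 60 women".

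**The concern.** The choice of primary outcome belongs in the protocol, and this protocol makes that choice: eight measures with equal standing. Its analysis section puts the before-after comparison beside the between-group comparison without ranking them. Nothing in the text would stop a single nominally significant result, on any one of the eight and from either comparison, being presented as a positive primary outcome.

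Two things are at stake. First, with several chances to succeed, the overall false-positive rate for the primary question is well above the level of any one test, so an isolated finding in 60 women would be hard to tell from chance. Second, the before-after comparison does not use the randomisation. Season, ageing, regression to the mean or a change in habits on joining a study can move a measure over 12 weeks in both arms. A before-after test would then be positive whether or not the supplement does anything.

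**Working it through.** **Inputs from the protocol.** Eight primary outcomes (section 5); between-group and before-after comparisons (section 7); 30 women per arm (section 3); primary outcomes measured at weeks 0 and 12 only (section 6), so repeated visits add no further primary tests.

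**Assumptions, because the protocol gives no figure.** Two-sided 5% per test with no adjustment; normally distributed outcomes; correlation between week 0 and week 12 of 0.7; a common correlation between outcomes of 0, 0.3, 0.5 or 0.7. The protocol has no error rate or power figure of its own to reproduce.

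**Step 1: independent tests.** The chance of at least one false positive in k independent tests is 1 − 0.95^k.
- k = 8 (one between-arm test per outcome): 1 − 0.95^8 = 0.337.
- k = 24 (adding a before-after test in each arm): 1 − 0.95^24 = 0.708.

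The second figure is too high when the between-arm test uses change scores, because that test is built from the same two within-arm changes as the before-after tests. The outcomes are also correlated with one another; T-CL, for example, contains HDL-C and LDL-C. Simulation allows for both.

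**Step 2: simulation under no effect and no time trend** (30 per arm, t tests on change from week 0 to week 12).

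| Correlation between outcomes | 8 between-arm tests | plus before-after tests in both arms (24 tests) |
|---|---|---|
| 0 | 34% | 63% |
| 0.3 | 30% | 57% |
| 0.5 | 26% | 50% |
| 0.7 | 20% | 40% |

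Repeat runs moved these figures by about one percentage point. If the between-arm test uses week-12 values instead of change, the right-hand column becomes about 70%, 65%, 57% and 47%. Chi-squared tests are left out: no cut-points are given, so their number and form cannot be fixed.

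**Step 3: before-after tests under a time trend.** Suppose every outcome drifts by an assumed 0.2 SD in both arms. The SD of a change score is √(2 × (1 − 0.7)) = 0.775, so the drift is 0.2 / 0.775 = 0.258 SD of change, or 0.258 × √30 = 1.41 standard errors in an arm of 30. With an assumed set of plausible correlations among the eight measures, before-after tests in the supplement arm alone gave at least one significant result in about 89% of trials with no supplement effect. The eight between-arm tests stayed near 30%.

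**Step 4: what control would cost.** Bonferroni over eight tests uses 0.05 / 8 = 0.00625 per test. The family-wise rate is then 1 − (1 − 0.00625)^8 = 0.049 if the tests are independent, and about 3% to 5% over the correlations above. Approximate power per outcome is Φ(d√(n/2) − z), with n = 30 and √15 = 3.873:
- d = 0.5 SD (assumed): 1.936 − 1.960 gives 49% at 0.05; 1.936 − 2.734 gives 21% at 0.00625.
- d = 0.8 SD (assumed): 3.098 − 1.960 gives 87% at 0.05; 3.098 − 2.734 gives 64% at 0.00625.

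**The case against.** The strongest reply is that much of this rests on silence. The protocol never says that tests are run at an unadjusted 5%, and a significance level and multiplicity method are commonly left to a statistical analysis plan, which is not at hand. That stands: a reader might infer unadjusted testing, but the text does not say it, and 5% here is an assumption. It does not dispose of the point. The unranked list of eight and the equal footing of the two comparisons are in the protocol itself.

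A reader might also infer that a false-positive primary result is more likely than not. For the randomised comparison alone this is not so: the rate runs from about 20% to 34%. It reaches or passes one half only when before-after tests also count and the outcomes are not strongly correlated. The overlap between T-CL and the other lipids lowers the rate.

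Nor does section 7 clearly require a chi-squared and a t test on every measure, or before-after tests in both arms. The sentence covers the primary measures collectively, so the 24-test count is one reading of it.

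Finally, the objectives are worded as investigation, not confirmation, and no power is claimed. That softens the consequence. A protocol that labels outcomes primary still needs to say what would count as a positive result.

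**Conclusion.** The point holds as a defect in what the protocol fixes: eight primary outcomes without rank, two kinds of comparison without rank, and no deciding result. At an assumed two-sided 5% per test, the false-positive risk for the primary set is about four to seven times the nominal level for the between-arm tests alone (20/5 = 4; 34/5 = 6.8). It is about eight to thirteen times that level if before-after tests in both arms count as well (40/5 = 8; 63/5 = 12.6). The second range depends on one reading of section 7, on change scores and on the assumed week 0 to week 12 correlation of 0.7. The weakness of before-after tests as evidence of a supplement effect depends on none of these figures, since they do not compare the randomised groups.

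**What to change.** In section 5, name one of the eight listed outcomes as primary; baPWV or visceral fat area would fit the stated objective. In section 7, make one between-arm comparison of that outcome, at two-sided 5%, the deciding test. List the other seven as secondary or exploratory.

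Alternatively, keep all eight as primary and state that Holm's procedure across the eight between-arm tests is the criterion for success.

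In either case, say that before-after results are descriptive.

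This changes wording only and needs no new data. Under the first option, seven outcomes lose primary status. Under the second, power per outcome drops: at 30 per arm with Bonferroni, from about 49% to 21% for an assumed 0.5 SD effect and from 87% to 64% for 0.8 SD, with Holm somewhat less severe. At this sample size that favours a single primary outcome.
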